**Figure 1 F1:**
[figure not shown]
Location of study communities: Gimbichu *woreda*, Oromia Region, Ethiopia.

The intervention was initiated on 30 April 2024 and data collection should be completed by mid-December 2024.

### Patient and public involvement

As indicated above, the research question was originally articulated by the Ethiopian Ministry of Health. The coauthors of this manuscript designed the study and selected the study communities following consultation with local Ministry of Health authorities. The field staff and local investigators then convened meetings with Ministry of Health personnel and residents of the study communities to explain the rationale, objectives and planned procedures of the study. Residents of the communities were not directly involved in the study design. The plan for dissemination of study results is described below.

### Inclusion, exclusion and withdrawal criteria

Non-pregnant women 18–49 years of age who are using a long-acting contraceptive (injectable or implanted hormonal contraceptive or intrauterine device) and who are not intending to move from the community or become pregnant during the subsequent 6 months will be eligible to participate in the trial if they agree to use only the salt provided by the project for the study duration and provide their informed consent, as indicated by signature or thumb print. In cases where there is more than one woman of reproductive age residing in the household or more than one household residing in the same physical structure, just one woman of reproductive age from that physical location will be randomly selected for participation.

Women who are currently pregnant or at risk of becoming pregnant (ie, not using contraceptives), and those who are unwilling to use the salt provided by the study or are planning to leave the study area within the next 6 months will be excluded from participation. In addition, women will be excluded if they are reportedly suffering from an acute or chronic disease (such as diarrhoea, intestinal malabsorption, chronic febrile illness, or metabolic or cardiovascular disorders) that might affect their dietary intake or folate status, as well as those who are using medications that can interfere with folate metabolism (antacids, inhaled or systemic corticosteroids, hydantoin derivatives, valproic acid derivatives, biguanides, bile acid sequesters, potassium-sparing diuretics). Consistent with national guidelines,^26^ women who have a mid-upper arm circumference <23 cm and are breastfeeding an infant <6 months of age will be referred to the local health system for treatment of undernutrition and will be excluded from the trial. Based on our preliminary studies, we do not expect women to be using vitamin-mineral supplements; but if any women are consuming supplements that contain folic acid, they will be excluded. Women who have hypertension (systolic pressure >140 or diastolic pressure >90) on two occasions on separate days will be referred to the local health centre for further evaluation and treatment and will be excluded from the trial. Women who are found to have macrocytic anaemia (Hb<132 g/L; mean corpuscular volume (MCV)>100 fL) at the time of the initial blood collection will be excluded from the trial and referred to the local health centre for further evaluation and possible treatment with folic acid and/or vitamin B_12_. Women who are found to have microcytic anaemia (Hb<132 g/L; MCV<80 fL) will be referred to the local health centre for presumptive treatment of iron deficiency and will remain eligible for the study. Women with mild, normocytic anaemia (Hb<132 g/L, ≥122 g/L) will be included in the study. Women with moderate/severe normocytic anaemia (Hb<122 g/L) will be excluded from the trial and referred for evaluation. All Hb cut-offs are adjusted for altitude.^27^

Women will be free to withdraw from the study at any time. In addition, women who are absent from the study community and are unable to consume the study-provided salt for more than 28 days (two consecutive or non-consecutive rounds of the biweekly salt delivery) will be dropped from the study. Participants who withdraw or are discontinued after randomisation will not be replaced. All data collected until the time of withdrawal will be included in the intention-to-treat analysis.

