#### Assessment of SAEs

SAEs are defined as any illness or disorder that results in death or long-term disability, or requires an overnight stay in a clinical facility, regardless of the nature of the condition.^53^ All SAEs will be recorded during the biweekly home visits and reported within 48 hours to the co-PIs, who will classify them as being ‘likely to be related to the intervention’ or ‘unlikely to be related to the intervention’. The co-PIs will share these findings with the IRB on a monthly schedule.

We have established an external Data and Safety Monitoring Board (DSMB) to review whether any SAEs occur more frequently in any of the study groups. The DSMB comprises an Ethiopian physician, a statistician, a nutritionist, a staff member of the Ethiopian Food and Drug Authority and a person with expertise in research ethics. A list of all SAEs will be recorded continuously for periodic review by the DSMB statistician, who is not participating in the core study team. The DSMB statistician will aggregate the SAEs by study arm for review by the DSMB. The review frequency will depend on the number of new SAEs occurring over time. The DSMB will have the authority to interrupt or stop the trial if there is a significant excess number of SAEs that may be related to the intervention in either folic acid group.

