### Data management and statistical analysis

For most types of data, information will be collected using automated (tablet-based) data entry with range checks and consistency checks incorporated into the data entry software. One exception is the dietary intake data, which will be recorded first on paper forms for preliminary review before entering the consolidated food intake data into the database.

Open Data Kit (ODK) software will be used for primary data collection.^57^ The records will be submitted to a web-accessible ODK aggregate database installed in a dedicated, secure server at EPHI. All sets of up-to-date raw data will be archived in comma-separated value (CSV) format. The archived data will be the aggregated data from each record that formed the basis for editing and analysis. First, all identifiable information will be removed and individual records will be coded just by the participant identification numbers. Deidentified raw data will be retained at EPHI and transferred to UC Davis weekly for editing, generating additional data reports and archiving.

The data managers at EPHI and UC Davis will jointly prepare the data editing syntax, which will be accessible to the appropriate co-investigators, along with the raw data and any data correction forms. Raw CSV data will be exported to STATA V.17 software, and data review and editing will be performed using the same software, for which STATA syntax will be developed. For errors, mistakes or missing data identified during data review, a separate data correction form will be completed and signed by the data collector, supervisor and field coordinator.

A detailed statistical analysis plan will be completed and posted publicly before the analysis is initiated. All study personnel will remain blinded to intervention group assignment (A, B or C) until investigators have reached agreement on result interpretation. Briefly, the data analysis will consist of descriptive analyses of sociodemographic data, anthropometry, blood pressure and vitamin and mineral status at baseline, followed by group-wise comparisons of change in folate and iodine status using both intention-to-treat and per protocol analyses. All data collected from women who subsequently withdraw from the study will be retained and included in the intention-to-treat analyses. Group-wise comparisons of possible adverse metabolic effects will be completed initially just in the control group versus higher folic acid group.

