Variable distributions will be described using means, prevalences and percentiles, as appropriate. Generally, intervention effects will be assessed using analysis of covariance models to estimate group mean differences for continuous outcomes controlling for baseline measurement. Models will be repeated in minimally adjusted and multivariable models to increase the precision of intervention effect estimation. A similar approach will be taken for categorical outcomes using log-binomial or modified Poisson regressions (dependent on model convergence) to estimate prevalence ratios across groups. Prespecified effect modification (eg, by baseline RBC folate concentration, markers of vitamin B_12_ status, genetic polymorphisms and selected household socioeconomic and demographic variables) will be assessed by incorporating interaction terms into the models, followed by regions of significance or stratified analyses to understand the nature of effect modification.

In addition to measuring the impact of the intervention, we will model the levels of folic acid intake necessary to achieve selected RBC folate concentrations. This will be done by using the distribution of RBC folate in the control group to characterise what distribution shift would be necessary to move nearly all (>95%) of the women above the target concentration to minimise the risk of NTDs. Next, the differences in final distributions between the control group and the two intervention groups will be used to interpolate what folic acid fortification level would achieve the desired distribution shift.

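### The 28-day absence rule ends follow-up itself, so the endline comparison labelled intention-to-treat covers only women who were not dropped

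*Protocol article*

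**What the plan says.** In the Protocol article, under Inclusion, exclusion and withdrawal criteria, the rule has two conditions, absence from the community and inability to take the study salt: a woman who meets both "for more than 28 days (two consecutive or non-consecutive rounds of the biweekly salt delivery) will be dropped from the study". The next sentences add that "Participants who withdraw or are discontinued after randomisation will not be replaced" and that "All data collected until the time of withdrawal will be included in the intention-to-treat analysis".

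Under Data management and statistical analysis, both intention-to-treat and per-protocol comparisons are promised for folate and iodine status, and the article says again that "All data collected from women who subsequently withdraw from the study will be retained and included in the intention-to-treat analyses". The general model is "analysis of covariance models to estimate group mean differences for continuous outcomes controlling for baseline measurement".

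Three other sections bear on this. Data collection procedures places the endline blood draw at weeks 24–26 and one intermediate draw at a random point in weeks 4–20. Assessment of SAEs says events are recorded at the biweekly home visits. The list of primary endpoints, under Study design, study site and randomisation, includes the period prevalence of SAEs. Nowhere does the article say that a dropped woman will still be asked for endline measurements or followed for SAEs.

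**The concern.** Absence that interrupts exposure is a post-randomisation event. It is a natural reason to leave a woman out of a per-protocol set. It is not a reason to stop measuring her, because an intention-to-treat comparison needs outcomes from women as randomised, whatever their later exposure. Here the woman leaves the study, not only the per-protocol set.

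Three things are at stake. First, the endline comparison labelled intention-to-treat leaves out a group selected for lower exposure, so it estimates something nearer to the effect under near-continuous availability of the salt. That matters in a trial that calls itself a hybrid of efficacy and effectiveness. Second, the contrast between the two promised analyses becomes less informative. Third, SAE observation time is cut short in dropped women, although SAEs are a primary endpoint. An analysis plan can choose how to handle missing values, but it cannot recover samples or event reports that the protocol stops collecting.

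**Working it through.** **The plan's own figure.** Inputs from Sample size estimates: difference 0.5 SD (89 nmol/L, SD 177.5), alpha 0.05, power 0.90. With a two-sided test, n = 2(1.960 + 1.282)²/0.5² = 84.1, rounded up to 85 per group. This matches the article. The three-arm adjustment is not specified. Alpha/2 gives 100 per group (101 with the t distribution), and dividing by 0.85 for attrition gives 118–119, close to the stated 120.

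**Loss at the planned attrition.** 0.15 × 120 = 18 women per arm (54 of 360), leaving 102. Power for 89 nmol/L with 102 per arm is 0.948 at alpha 0.05 and 0.910 at alpha 0.025. The issue is who is analysed, not how many.

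**How strict the rule is.** 26 weeks is 182 days, and 28/182 = 15.4%. A woman just past the limit may still have had the salt for 84.6% of the trial.

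**Illustration of the bias.** Let f be the share dropped and r the share of the 89 nmol/L effect that dropped women would show at endline. Both are assumptions. The article gives only 15% attrition from all causes. With dropped women otherwise like the rest:

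all-randomised effect = 89 × [(1 − f) + f × r]; overstatement by completers = 89 / that value − 1.

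| f | r = 0 | r = 0.5 | r = 0.846 |
|---|---|---|---|
| 5% | 84.55 (5.3%) | 86.78 (2.6%) | 88.31 (0.8%) |
| 10% | 80.10 (11.1%) | 84.55 (5.3%) | 87.63 (1.6%) |
| 15% | 75.65 (17.6%) | 82.33 (8.1%) | 86.94 (2.4%) |

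The entries are nmol/L, with the overstatement in brackets. The value r = 0.846 takes the effect as proportional to days exposed for a woman just past the limit.

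The absolute overstatement runs from 89 − 88.31 = 0.69 to 89 − 75.65 = 13.35 nmol/L. The standard error of an unadjusted difference with 102 per arm is 177.5 × √(2/102) = 24.9, so this is about 0.03 to 0.54 standard errors.

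**Check by simulation.** This used a baseline-adjusted ANCOVA with 120 per arm and an assumed baseline–endline correlation of 0.6. With 15% dropped in both arms, all-randomised versus completer estimates were 81.9 versus 88.6 (r = 0.5), 75.9 versus 89.2 (r = 0) and 88.4 versus 88.4 (r = 1). The formula is confirmed, and the bias vanishes if dropped women respond like the rest.

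**The threshold.** Two biweekly rounds make exactly 28 days, whereas the sentence says more than 28. These are different limits.

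**The case against.** The strongest reply is that the article promises only to use data collected before withdrawal, and that promise can be kept. Salt disappearance and SAEs recorded before a woman is dropped do enter the analysis. The women concerned may also be few, since those planning to move or leave within six months are excluded at entry. Both points stand. The first does not help the endline biomarkers, which do not exist for a woman dropped before week 24. The second bears on size, not on principle.

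Several stronger readings are tempting but not supported:

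- A reader might infer that the ANCOVA shuts out every woman without an endline value and wastes the intermediate draw. The article describes ANCOVA only as the general approach, in a brief summary, and defers detail to an analysis plan that is not shown. That plan could use the intermediate sample.
- A reader might infer that the analysed set is selected on adherence. The trigger requires absence from the community. A woman at home who uses little study salt, or other salt, is not dropped, so the intention-to-treat and per-protocol sets can still differ.
- Because an SAE includes any illness that "requires an overnight stay in a clinical facility, regardless of the nature of the condition", a reader might infer that a long admission both counts as an SAE and hides later ones. If period prevalence is counted per woman, she is already in the numerator. What is lost is observation time in women dropped for other reasons.
- A reader might suppose that loss differs by arm. For example, with 10% against 20% lost and lost women 89 nmol/L lower, the bias from this source would be (0.20 − 0.10) × 89 = 8.9 nmol/L. All arms receive coded iodised salt. A slight colour difference is admitted, but nothing suggests that absence depends on arm.
- The 15% attrition allowance covers all causes. Assigning all of it to this rule gives an upper illustration, not an estimate.

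**Conclusion.** The point holds in a limited form. The rule turns a per-protocol criterion into an end of follow-up, so the endline biomarker comparison called intention-to-treat is restricted to women not dropped, and SAE observation is truncated for the others. This follows from the text and does not depend on what the analysis plan contains.

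The size is not known. Under the assumed ranges (5–15% dropped, 0–85% of the effect retained, no other difference between dropped and remaining women), the overstatement is about 1% to 18%. It is 0.8% to 2.4% if dropped women are only just past the limit, and it could be negligible if few are dropped. Power is not a concern. This is a worthwhile, inexpensive improvement and not a defect that invalidates the trial.

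**What to change.** - Use the 28-day rule only to define the per-protocol set.
- Unless consent is withdrawn, keep these women in SAE follow-up, invite them to the scheduled intermediate and endline measurements, and analyse them in the arm to which they were randomised.
- Let women with only an intermediate sample contribute through a longitudinal sensitivity analysis that accounts for the week of sampling.
- Whether study salt continues after a long absence is a separate question for the investigators. The point here concerns measurement only.
- Reconcile the limit of more than 28 days with the limit of two rounds.
- The article gives 30 April 2024 as the start and mid-December 2024 as the expected end of collection. If collection is complete, label the endline analysis as completer-based, report the number and timing of drops by arm, and add the longitudinal sensitivity analysis.

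The cost is a short amendment and some tracing effort. The measurements are already scheduled for every randomised woman, and the required sample size does not change. The estimate would be slightly diluted. With all 120 per arm measured, power stays at 0.91–0.97 at alpha 0.05 over the range in the table, and at 0.86–0.95 at alpha 0.025.

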### Recruitment of study participants

Using existing household listings, members of the study team will contact a convenience sample of previously identified WRA at their homes to explain the purpose, methods, benefits, inconveniences and risks of the research, and to assess the women’s eligibility and seek their consent to participate. After presenting a disclosure statement and request to proceed with the interview, the data collector will obtain information from verbally consenting women on their age, pregnancy status, contraception practices, education, religion, ethnicity, employment and general health status; household location (GPS coordinates); plans to remain in the study community; housing characteristics (construction materials, water source, sanitary facilities, access to electricity and cellphone service); cellphone number (if available); selected household assets, main source(s) of household income and potential willingness to participate in the subsequent research studies. The data collector will also measure the women’s blood pressure, review the women’s health history and determine their potential eligibility for the study. For women who are potentially eligible to participate, the data collector will describe the purposes of the intervention trial, the study procedures and related risks and benefits, the confidentiality of results and the fact that participation is voluntary. After providing an opportunity for women to consult with family members and ask any questions, the field worker will request signed consent from the women to participate in the intervention trial. The women then will be invited to attend the local health post for additional screening, including a second blood pressure assessment, anaemia assessment and a urinary pregnancy test.

### Informed consent, institutional review board approval and trial registration

For the initial home visit to screen WRA for eligibility, a disclosure statement will describe the components of the interview, and verbal consent will be requested by the data collector before proceeding with the interview. For the intervention trial, signed consent will be required. Printed consent forms prepared in the local language, Afaan Oromo (Oromiffa), will be read aloud by the data collectors to individuals who are considering participation in the study. A participant advocate who is not part of the research team will be present during the consent procedures and will cosign the forms as a witness. The consent form describes how the data will be protected to ensure confidentiality and the possible use of deidentified data and stored biological specimens for future research.

The study protocol was submitted to the institutional review boards (IRB) at the Ethiopian Public Health Institute (EPHI) and the University of California Davis (UC Davis). The EPHI IRB approved the study (including both the preliminary investigations and the intervention trial) on 2 June 2023 (protocol number EPHI-IRB-494-2023). Following its review of the protocol (Project No 2078626-1) and examination of documents from the EPHI IRB, the UC Davis IRB determined on 18 September 2023 that separate approval from UC Davis was not required. The trial protocol has been registered with the ClinicalTrials.gov website (registration number NCT06223854).

Study participants will receive the study salts for free, and they will be compensated in kind with sanitary products, like soaps, and other small (non-monetary) gifts.

### Intervention

Households of WRA will be randomly assigned to one of three study arms to receive salt fortified with: (1) a lower dose of folic acid+iodine, (2) a higher dose of folic acid+iodine or (3) iodine only (comparator group). Based on the results of preliminary studies of discretionary salt intake in the study communities, the amount of folic acid in the two DFS will be 30 ppm for the lower dose arm and 90 ppm for the higher dose arm to provide average additional folic acid intakes of ~200 μg/day or ~600 μg/day, respectively, in the two folic acid groups. These amounts of additional folic acid intake are intended to span a range of intakes that should increase RBC folate concentration, as indicated by a previous folic acid supplementation trial,^28^ and should not result in excessive folic acid intake.^29^ This dose–response design will also permit subsequent modelling to determine the appropriate level of folic acid fortification needed to achieve a desired RBC folate concentration in the local context. We recognise that minor losses of folic acid may occur during storage of DFS-IoFA ([name], unpublished),^30^ so the target fortification levels account for this. We also note that folic acid is sensitive to different types of cooking, related cooking temperatures and duration of thermal exposure.^31 32^ Nevertheless, most folic acid is retained during cooking of fortified flours and rice, regardless of the type of cooking, and flour fortification programmes have succeeded in reducing NTDs despite the effects of cooking. Thus, we expect to be able to detect a nutritional response to the folic acid-fortified salt.

Following systematic inspection of national salt production facilities, a multistakeholder advisory panel selected Green Star Trading, Hawassa, Ethiopia, to produce the study salts. Project managers from the Nutrition International Ethiopia Country Office will indicate the code letters (A, B or C) to be applied to the three types of salts. These codes will be retained by Nutrition International (NI) and the salt producer, and will be stored in sealed envelopes in locked filing cabinets of the two co-PIs who will not be informed of the salt codes until the data collection and preliminary analyses are completed. The salt production, fortification and quality assurance procedures are described in a separate procedures manual available from NI. As per Ethiopian standards for iodine content, the refined salt used for this study will contain 30–40 ppm iodine as potassium iodate. Both fortificants (iodate and folic acid) will be added simultaneously using the current spray technology used by the production plant. The salt will be packaged in opaque, plastic containers containing 500 g salt, with labels stating that the salt is iodised, may or may not contain vitamin B_9_ and is being distributed for research purchases only (see figure 2 for example of label).

